**5.16. Assessments to be completed by visit**

Standard procedures for each assessment are listed in the Manual of Procedures.

| Assessment                                               | Phone Screening | Screening | V1: Baseline | V2 & V5a: Spectacle dispensing
(On indication after V3-6) | V3 & V5b: 1-month after spectacles dispensing | V4-6: 6-monthly | V7: 24-month |
|----------------------------------------------------------|-----------------|-----------|--------------|--------------------------------------------------------------|-----------------------------------------------|-----------------|--------------|
| Informed consent/assent                                  |                 |           | X            |                                                              |                                               |                 |              |
| Demographics                                             | X               | X         |              |                                                              |                                               |                 |              |
| Medical history                                          | X               | X         | X            | X                                                            | X                                             | X               | X            |
| Refractive status history (last 2 years)                 | X               | X         |              |                                                              |                                               |                 |              |
| Myopia risk factor questionnaire                         |                 |           | X            |                                                              |                                               |                 |              |
| Randomisation                                            |                 |           | X            |                                                              |                                               |                 |              |
| Administer study intervention                            |                 |           |              | X                                                            |                                               | (X)             |              |
| VA by ETDRS (habitual/unaided; Distance & Near) (>6 yo)  |                 |           | X            |                                                              | X                                             | X               | X            |
| VA by HOTVUX (habitual/unaided; Distance & Near) (4-6yo) |                 |           | X            |                                                              | X                                             | X               | X            |

|                                                             |  |   |   |   |   |   |   |
|-------------------------------------------------------------|--|---|---|---|---|---|---|
| Cover test                                                  |  | X |   |   |   |   |   |
| Colour vision                                               |  | X |   |   |   |   |   |
| Interpupillary distance                                     |  |   | X |   |   | X | X |
| Non-cycloplegic autorefraction and keratometry              |  |   | X |   | X | X | X |
| Non-cycloplegic subjective refraction (>6 yo)               |  |   | X |   |   | X | X |
| Non-cycloplegic objective refraction by retinoscopy (4-6yo) |  |   | X |   |   | X | X |
| BCVA by ETDRS (Distance & Near) (>6 yo)                     |  |   | X |   |   | X | X |
| BCVA by HOTVUX (Distance & Near) (4-6yo)                    |  |   | X |   |   | X | X |
| BCVA by low contrast ETDRS OU (>6 yo)                       |  |   | X |   |   |   |   |
| BCVA by low contrast HOTVUX OU (4-6yo)                      |  |   | X |   |   |   |   |
| VA with new spectacles by ETDRS (>6 yo)                     |  |   |   | X |   |   |   |
| VA with new spectacles by HOTVUX (4-6yo)                    |  |   |   | X |   |   |   |
| VA with new spectacles by low contrast ETDRS OU (>6 yo)     |  |   |   | X |   |   |   |
| VA with new spectacles by low contrast HOTVUX OU (4-6yo)    |  |   |   | X |   |   |   |
| Phoria                                                      |  |   | X |   |   | X | X |
| Anterior ocular health                                      |  | X | X |   |   | X | X |
| IOP                                                         |  |   | X |   |   | X | X |
| Pupil size                                                  |  |   | X |   |   | X | X |
| Stereopsis                                                  |  | X | X |   |   |   |   |
| Amplitude of accommodation                                  |  |   | X |   |   | X | X |
| Accommodative lag                                           |  |   | X |   |   | X | X |
| OCT                                                         |  |   |   | X | X | X | X |

|                                                         |  |   |   |   |     |     |     |
|---------------------------------------------------------|--|---|---|---|-----|-----|-----|
| Cycloplegia                                             |  |   | X |   |     | X   | X   |
| Cycloplegic autorefraction                              |  |   | X |   |     | X   | X   |
| Peripheral refraction                                   |  |   | X |   |     | X   | X   |
| Cycloplegic subjective refraction (>6 yo)               |  |   | X |   |     | X   | X   |
| Cycloplegic objective refraction by retinoscopy (4-6yo) |  |   | X |   |     | X   | X   |
| Axial length                                            |  |   | X |   |     | X   | X   |
| Internal ocular health (central & periphery)            |  |   | X |   |     |     | X   |
| Fundus photo                                            |  |   | X |   |     |     | X   |
| Order spectacle lenses                                  |  |   | X |   |     | (X) | (X) |
| Verification of spectacle lenses                        |  |   |   | X | X   | X   | X   |
| Frame adjustment                                        |  |   |   | X | (X) | (X) | (X) |
| Spectacle lenses dispense                               |  |   |   | X |     |     |     |
| Visual performance questionnaire                        |  |   |   |   | X   |     |     |
| Treatment compliance                                    |  |   |   |   | X   | X   | X   |
| Adverse event review and evaluation                     |  |   | X | X | X   | X   | X   |
| Complete CRF                                            |  | X | X | X | X   | X   | X   |

### 5.17. Data collection schedules

The following steps will be conducted by study Investigators:

#### 5.17.1. V1: Eligibility, randomisation and baseline assessment

1. Screen potential participants over the telephone (recorded in electronic spreadsheet)
2. Enter contact details, demographics, and record refractive history (recorded in electronic spreadsheet)
3. Perform baseline assessment on participants for eligibility (recorded in REDCap CRF\_V1)
4. Randomisation of participant (recorded in electronic spreadsheet)

#### 5.17.2. V2 & V5a: Dispense

1. Order the type of spectacle lenses (SV/D1/D2 lenses) after V1 according to randomisation
2. Dispense treatment spectacles (recorded in REDCap CRF\_V2 & REDCap CRF\_V5a)

#### 5.17.3. V3 & V5b: Adaption

1. Measure visual performance (recorded in Qualtrics Survey)
2. Record treatment compliance (recorded in REDCap CRF\_V3 & REDCap CRF\_V5b)
3. Perform choroidal thickness measurement

#### 5.17.4. V 4-7: Follow-up assessments (data related to treatment outcomes)

The following steps will be completed by study Investigators at the 6, 12, 18 and 24-month follow-up visits:

1. Record results of follow-up visual assessments (recorded in REDCap CRF\_V4-7)
2. Record treatment compliance (recorded in REDCap CRF\_V4-7)
3. Record any adverse events affecting the participant and any incidental events (recorded in REDCap CRF\_AE)
4. Update spectacle lenses if required (recorded in REDCap CRF\_V2 & V5a)

### **5.18. Protocol violations**

A deviation from the protocol when no amendment has been submitted and approved would be regarded as a protocol violation. All protocol violations must be documented and reported (recorded in electronic spreadsheets). The prescribed treatment dose is at least 10 hours of spectacle wear per day, 7 days a week (i.e., at least 70 hours each week). A subject is considered as compliant with the study protocol if he/she has worn the spectacles for at least 56 hours a week (7 days of at least 8 hours each). If the spectacle lenses are worn for less than 35 hours per week or for less than 3 days per week, it is defined as a protocol violation. A list of such subjects will be prepared prior to unmasking.

## 6. Statistical Considerations

### 6.1. Sample Size Calculation

To achieve a 90% power to detect a 0.315D difference and standard deviation of 0.475D (effect size of 0.658) in SER progression between a treatment group and a control group with an alpha level of 0.05 (2-tailed); the minimum subject number required in each group was 50.

An interim analysis will be performed to evaluate the efficacy on primary and second outcomes at 6 months. To compensate for the impact on the final efficacy analysis, Bonferroni adjustment will be performed with an adjusted alpha level of 0.025. Accordingly, the subject number required in each group is 59 at a 90% power. Assuming a dropout rate of about 10%, at least 65 subjects are required in each group.

### 6.2. Statistical analysis

Data from the right eyes will be used for analyses when both eyes show fast progression. If only one eye demonstrated fast progression, that specific eye would be used for analyses. Demographic and optometric data will be displayed as mean and standard deviation, or number and percentage as appropriate. The Chi-square test (or if appropriate, Fisher's Exact test) and unpaired t-test will be performed to compare baseline between-group differences in demographics (age, sex). Myopia progression will be calculated as the difference between SER and AL at the baseline, the 6-month and the 1-year visits, respectively.

The unpaired t-test will be used to compare the changes in primary and secondary outcomes between groups. The efficacy of myopia control of DIMS lens will be determined by dividing the difference in myopia progression (or axial elongation) between two groups with the myopia progression (or axial elongation) in the SV group, then multiplied by 100%. Multiple regression analysis will be employed to identify factors that may be associated with myopia control efficacy. Regarding visual performance and comfort, subjective ratings collected by questionnaires will be compared between groups using Mann-Whitney U test.

Treatment will be discontinued if any treatment-related adverse event arises, such as constant visual disturbance (e.g., ghosting, diplopia, glare, etc.). The number of subjects

discontinuing treatment prematurely for any reason will be summarised by reasons for discontinuation. The incidence of all serious adverse events will be summarised.

Data analysis will follow an intention-to-treat approach. Missing values of outcome variables and covariates will be replaced using multiple imputation procedures with 10 sets of imputations assuming missing at random. All analyses will be 2-tailed with a significance level of 2.5%.

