## 5. Study Design

### 5.1. Inclusion criteria

The study will enroll participants aged between 4 and 12 years and of Hong Kong Chinese descent. Both eyes of the subjects should have a SER of -0.75D or lower. Except for children aged 4-6 years, documented evidence of fast progressing myopia over the past 2 years, either in terms of SER or AL, is required for enrollment. Documented evidence is defined as past prescription (Rx) forms issued by registered optometrist or registered ophthalmologist within 2 years before the baseline date. Fast progression is defined as a SER progression at a rate of 0.50D/year or more, or an AL elongation at a rate of 0.27mm/year or more in either or both eyes. Documented evidence is selected using the decision tree outlined below.

For children aged 4-6 years without past Rx forms, eligibility requires myopia below the 3rd percentile on refraction curves. Specifically, for 4 to 5-year-olds, their myopia should be -0.75D or below in both eyes. For 6-year-olds, their myopia should be -1.25D or below in at least one eye, with the other eye at -0.75D or below.

BCVA in both eyes should match age norms. For children aged 4-6 years, BCVA of 0.20 logMAR (or its equivalent) or better is necessary, whereas children aged 7-12 years should have BCVA of 0.00 logMAR (or its equivalent) or better. Anisometropia should not exceed 1.50D, and astigmatism should be equal to or less than 2.00D. Participants must demonstrate a willingness to accept random group allocation and adhere to the masked study design. Moreover, they should be able to wear the prescribed spectacles full-time.

[figure not shown]

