- **Cycloplegia:** One drop of Alcaine 0.5% or Provan 0.5% (topical anaesthetic) and 1 drop of Cyclopentolate hydrochloride 1.0% (antimuscarinic eye drop) will be instilled to induce cycloplegia. The effect of the cycloplegia will be evaluated by means of amplitude of accommodation (push-up method); if the amplitude of accommodation is more than +2.00D, then a second drop of 1% Cyclopentolate will be instilled. The remaining tests of this section will be performed under cycloplegia.
- **Cycloplegic autorefraction:** same procedure as the non-cycloplegic autorefraction.
- **Peripheral refraction:** measured by using a Shin-Nippon NVision-K 5001 autorefractor at center, 10°, 20° and 30° of the nasal and temporal visual field across the horizontal meridian in the right eye (if both eyes confirm fast progress) or in the fast-progress eye (if only 1 eye confirmed fast progress). Five measurements will be taken and averaged.
- **Cycloplegic subjective refraction:** same procedure as the non-cycloplegic subjective refraction.
- **Axial length:** measured by ZEISS IOLMaster 500.
- **Dilated fundus ophthalmoscopy:** posterior eye health will be checked using a binocular indirect ophthalmoscopy and fundus photo camera.

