#### 5.12. Primary outcome measure

The primary outcome will be the change in SER from baseline to 12 months, as measured by cycloplegic autorefraction (Shin-Nippon open-field autorefractor) in both eyes.

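### The analysis-eye rule, and the matching rule for baseline peripheral refraction, assign no eye to 4-6-year-olds admitted on the refraction centile without past prescription forms

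*Protocol*

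**What the plan says.** **Eye analysed.** Protocol 6.2, repeated in Section 1, has two branches. The first takes the right side by default: "Data from the right eyes will be used for analyses when both eyes show fast progression". The second branch deals with children in whom a single eye qualifies, and it reads: "If only one eye demonstrated fast progression, that specific eye would be used for analyses".

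**What fast progression means.** Section 5.1 gives it as a yearly rate: "Fast progression is defined as a SER progression at a rate of 0.50D/year or more, or an AL elongation at a rate of 0.27mm/year". The AL figure is likewise a minimum, and one qualifying eye is enough. The record behind the rate is also defined there: "Documented evidence is defined as past prescription (Rx) forms issued by registered optometrist or registered ophthalmologist within 2 years before the baseline date".

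**The other way in.** Section 5.1 exempts children aged 4-6 from documented progression. Those without forms enter on a cut-off at the third centile of a refraction curve; the sentence opens "For children aged 4-6 years without past Rx forms, eligibility requires myopia below the". At 4-5 years both eyes must be at -0.75 D or below. At 6 years at least one eye must be at -1.25 D or below and the other at -0.75 D or below.

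**Peripheral refraction.** At baseline (5.11) it is measured "in the right eye (if both eyes confirm fast progress) or in the fast-progress eye (if only 1 eye confirmed fast progress"). At 6, 12, 18 and 24 months (5.14) it is measured in the right eye, with no condition.

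**Primary outcome.** Section 5.12: "The primary outcome will be the change in SER from baseline to 12 months, as measured by cycloplegic autorefraction (Shin-Nippon open-field autorefractor) in both eyes".

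**The concern.** The eye rule depends on a quantity that one of the protocol's own entry routes does not produce. A child admitted on the centile has one refraction per eye at one date and no rate, so neither eye has been shown to progress fast.

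Two things are at stake.

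- **Primary analysis.** SER is measured in both eyes, so someone must choose one of them for these children. If no rule exists beforehand, the choice can be made with both eyes' outcomes in view. An efficacy look is planned at 6 months (6.1), and 8.7 sets up no independent monitoring committee.
- **Baseline peripheral refraction.** Only one eye is measured, and the site must pick it at V1. If the analysis later uses the other eye, the baseline value cannot be recovered. Whether baseline relative peripheral refraction influences the outcome is a stated secondary objective (Section 4).

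**Working it through.** **1. Entry routes against the two branches of 6.2 and 5.11**

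| Entry route (5.1) | Progression rate per eye? | Eye assigned? |
|---|---|---|
| Age 7-12, forms required | Yes | Yes |
| Age 4-6, forms showing fast progression | Yes | Yes |
| Age 4-5, no forms, both eyes at -0.75 D or below | No | No |
| Age 6, no forms, at least one eye at -1.25 D or below | No | No |

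No other section fills the last two rows. The decision tree in 5.1 is not reproduced in the text available, but 5.1 describes it as the means of selecting documented evidence, which these children do not have.

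**2. Upper limit on the share affected**

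The plan's group sizes serve only as denominators. With the stated effect size of 0.658, a two-sample t-test at two-sided alpha 0.025 and 90% power needs 58.6 per group, rounded up to the stated 59. The stated 65 is 59 × 1.10 = 64.9, rounded up.

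- Age mix 1:2:1 (Section 1 and 5.7): 4-6 stratum = 1/(1+2+1) = 25%.
- Per group of 65: 65 × 0.25 = 16.25, about 16 children.
- Of the 177 in Section 1: 177 × 0.25 = 44.25, about 44.
- Of three groups of 65: 195 × 0.25 = 48.75, about 49.

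Let f be the fraction of the stratum without forms. The protocol does not give f, so the whole range is shown. Share with no eye assigned = 25% × f.

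| f (assumed) | Share of trial | Of 195 (unrounded) |
|---|---|---|
| 0 | 0% | 0 |
| 0.25 | 6.25% | 12.2 |
| 0.50 | 12.5% | 24.4 |
| 0.75 | 18.75% | 36.6 |
| 1.00 | 25% | 48.75 |

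**3. Where the choice of default changes the eye**

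Take two candidate defaults for these children: always the right eye, or the eye meeting the age threshold (right if both do).

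- Age 4-5: both eyes meet -0.75 D by definition of entry, so both defaults give the right eye.
- Age 6, both eyes at -1.25 D or below: right eye under both.
- Age 6, only the right eye at -1.25 D or below: right eye under both.
- Age 6, only the left eye at -1.25 D or below: right eye under one default, left under the other.

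Only the last case differs. If ages are spread evenly over 4, 5 and 6 (assumption), all 6-year-olds together are 25%/3 = 8.3% of the trial, before removing those with forms or with a qualifying right eye.

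**4. Baseline against follow-up peripheral refraction**

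Take a child of any age whose left eye alone is fast. Section 5.11 measures the left eye at baseline; 5.14 measures the right eye at every later visit. Change in relative peripheral refraction, listed as an outcome in Section 1, would then compare two different eyes. This conflict is not confined to the 4-6 stratum.

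**The case against.** **The eye could be settled in an SAP before unmasking.** For SER this is true: both eyes are measured and the eye can be derived from baseline data. It does not help peripheral refraction, where the site chooses one eye at V1. Nor is this detail merely deferred, since the protocol fixes a rule and that rule omits one of its own entry routes.

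**The practical ambiguity is small.** If the centile criterion is taken to stand in for fast progression, the two natural defaults part only for some 6-year-olds. This stands and limits the size of the problem. But the protocol does not say that the centile stands in for progression, so the sentence is still needed.

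**Assessors are masked and any eye rule would apply to both arms.** Also fair. No direction or size of bias can be shown; what can be shown is that the choice is left open.

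**Stronger readings that the document does not support:**

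- *A quarter of the trial has no analysis eye.* That needs every 4-6-year-old to lack forms. Those with forms showing fast progression are covered, and the fraction is not given.
- *Power falls because these children leave the analysis.* That needs the deletion of children whose SER is measured in both eyes, under a plan that specifies intention-to-treat and multiple imputation.
- *5.12 and 6.2 set two rival primary endpoints.* Section 5.12 says the outcome is "as measured by cycloplegic autorefraction (Shin-Nippon open-field autorefractor) in both eyes", which can be read as the eyes measured, while 6.2 says which data are analysed. Section 6.2 describes no two-eye analysis. The wording should be aligned, but a contradiction is not established.

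**Conclusion.** The gap is real. The eye rule in 6.2 and Section 1, and its counterpart in 5.11, do not cover children aged 4-6 admitted on the centile without forms. The affected share lies between 0% and 25%, depending on a fraction that the protocol does not state; 25% is a ceiling and rests on the planned 1:2:1 age mix being achieved. The consequences are an open choice of analysis eye that could be made after outcomes are known, and a baseline peripheral refraction that may come from an eye not analysed. The unconditional right eye in 5.14 is a separate, definite mismatch with 5.11. The wording of 5.12 is a lesser point of clarity.

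**What to change.** 1. **6.2, Section 1 and 5.11:** add a branch that uses baseline data only. For a child admitted on the centile rule, use the right eye if both eyes meet the age threshold in 5.1, otherwise the eye that meets it. Apply it to the same baseline refraction on which eligibility was judged.
2. **CRF_V1:** add a field for the analysis eye, completed before randomisation. Section 5.17.1 already places the baseline assessment before randomisation, so the order of steps does not change.
3. **5.12:** say that SER is measured in both eyes and that the primary outcome is the 12-month change in the analysis eye.
4. **5.14:** measure follow-up peripheral refraction in the eye selected under 5.11, so that baseline and follow-up come from the same eye.

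A sensitivity analysis on the mean of both eyes is possible with data already collected, but is optional.

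The cost is wording in five places and one CRF field. No measurement is added. For children already enrolled on the centile route, the same baseline-only rule can be applied to their recorded V1 refraction, and any child whose baseline peripheral refraction was taken in the other eye should be listed before outcome data are examined.

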## Randomisation

After baseline measurements, subjects will be Randomised to three groups at a ratio of 1:1 using a stratified randomisation based on age. Age will be stratified into 3 groups: 4-6, 7-9, and 10-12, in a ratio of 1:2:1.

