## **5.7. Randomisation**

Simple randomisation will be implemented by an unmasked Investigator by creating a column of random numbers for the group allocation using Microsoft Excel. Eligible subjects will be assigned to one of the three groups in an equal ratio by following the random sequence generated from Excel. Age will be stratified by 3 groups: 4-6, 7-9 and 10-12, in a ratio of 1:2:1.

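### The primary comparison is an unadjusted t-test although age and baseline refraction are available, and age is a declared stratification factor: the cost is lost efficiency, not invalidity

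*Protocol*

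**What the plan says.** - **Primary endpoint** (section 5.12): "The primary outcome will be the change in SER from baseline to 12 months", measured by cycloplegic autorefraction. Axial length change over the same period is secondary (section 5.13).
- **Test** (section 6.2, same in section 1): "The unpaired t-test will be used to compare the changes in primary and secondary outcomes between groups". No covariate or stratum is named.
- **Regression** (section 6.2) has another purpose: "Multiple regression analysis will be employed to identify factors that may be associated with myopia control efficacy".
- **Allocation, section 1**: randomisation is "using a stratified randomisation based on age", and "Age will be stratified into 3 groups: 4-6, 7-9, and 10-12, in a ratio of 1:2:1".
- **Allocation, section 5.7**: "Simple randomisation will be implemented by an unmasked Investigator", from a column of random numbers in Excel. The same section adds: "Age will be stratified by 3 groups: 4-6, 7-9 and 10-12, in a ratio of 1:2:1".
- **Covariates at hand**: section 5.11 and the visit table in 5.16 collect age, cycloplegic autorefraction ("same procedure as the non-cycloplegic autorefraction") and axial length by V1.
- **Sample size** (section 6.1): 0.315 D difference, SD 0.475 D, effect size 0.658, 90% power, two-sided alpha 0.025 after the interim adjustment, 59 evaluable per group.

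**The concern.** The trial enrols children aged 4 to 12, describes younger myopes in section 3 as an under-studied group, and names age as its only stratification factor. It then leaves age out of the comparison that decides the trial, and leaves out the baseline value as well. If either predicts 12-month change, an adjusted analysis gives a smaller standard error at no cost in recruitment. If allocation is also balanced within age strata, the t-test charges to error some variation that the design has already removed, so its nominal 2.5% level is not the level at which it operates. At stake are narrower confidence intervals, some power, and an analysis that matches the design.

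**Working it through.** **Reproducing the plan's figure.** With the noncentral t-distribution and effect size 0.658, the required number per group is 49.5, rounded up to 50, at alpha 0.05, and 58.6, rounded up to 59, at alpha 0.025. Both match section 6.1. Power at 59 per group is 90.2%. (0.315/0.475 is 0.663, which gives 49, 58 and 90.7%; the difference has no consequence here.)

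**Assumption.** R² is the share of variance in 12-month SER change explained by the covariates. The protocol gives none, so 0.10 to 0.25 is used, with 0.30 as an outer value.

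**Formulas, 59 per group, two-sided alpha 0.025.**
- Unadjusted standard error: 0.475 × √(2/59) = 0.0875 D.
- Adjusted standard error: 0.0875 × √(1 − R²). This is 5% smaller at R² 0.10 and 13% smaller at 0.25.
- Adjusted power: noncentral t with effect size 0.658/√(1 − R²), that is 0.694 at R² 0.10 and 0.760 at 0.25. The few degrees of freedom spent on covariates are ignored.
- t-test, simple allocation: standard error correct, power 90.2% whatever R² is.
- t-test, arms balanced within strata and R² due to age stratum: the estimate varies with SD 0.0875 × √(1 − R²), but the test still divides by about 0.0875. Hence true alpha = 2 × [1 − Φ(2.241/√(1 − R²))]. Power = Φ[(0.658 × √(59/2) − 2.270)/√(1 − R²)] = Φ[1.304/√(1 − R²)], where 2.270 is the t critical value on 116 degrees of freedom.

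| R² | Adjusted SE (D) | Adjusted power | t-test power, simple | t-test power, balanced | t-test true alpha, balanced |
|---|---|---|---|---|---|
| 0.10 | 0.0830 | 93.1% | 90.2% | 91.5% | 0.018 |
| 0.25 | 0.0757 | 96.7% | 90.2% | 93.4% | 0.010 |
| 0.30 | 0.0732 | 97.6% | 90.2% | 94.0% | 0.007 |

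The gain from adjustment is therefore about 1.6 to 3.3 points with balanced strata and 2.9 to 6.5 points with simple allocation, for R² 0.10 to 0.25. Only under simple allocation can the gain be read as 59/0.90 = 65.6 to 59/0.75 = 78.7 unadjusted children per group, or about 7 to 20 more.

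**Simulation check** (4,000 trials per scenario, 59 per arm, strata about 1:2:1, difference 0.315 D, SD 0.475 D, R² 0.10, 0.20 and 0.30).
- Balanced strata: the t-test's mean standard error stayed near 0.087 D, while its estimate had a true SD of about 0.081-0.082, 0.079 and 0.074 D. Type I error was 0.019, 0.015 and 0.007. Power, t-test against adjusted, was 91.8% vs 93.5%, 92.8% vs 95.9% and 94.4% vs 97.8%.
- Simple allocation: the true SD was about 0.087-0.088 D, matching the reported standard error. Type I error was 0.026, 0.030 and 0.026, with a Monte Carlo standard error of √(0.025 × 0.975/4000) = 0.0025. Power was 91.4% vs 93.4%, 90.6% vs 95.8% and 90.7% vs 97.9%.

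**The case against.** The strongest reply is that nothing here is wrong in the sense of validity. Under randomisation the unadjusted difference is unbiased, its type I error is at or below nominal, and the sample size was built on this very test and meets its target. All of that stands. Chance age imbalance under simple allocation is real for a single trial, but the t-test's error rate already allows for it.

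Three stronger readings are tempting, and the protocol does not support them.

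- *The standard error is too large.* This needs arms balanced within age strata. Section 5.7 calls the randomisation simple, the document mentions no blocks or other balancing device, and section 1 (study population) uses the same 1:2:1 ratio in a way that could be an enrolment quota. Under simple allocation the standard error is correct for the estimator and the test is not conservative.
- *The plan loses both the full power gain and the alpha.* These belong to different schemes. With balanced strata the t-test itself gains power, so adjustment adds less; with simple allocation alpha is not lowered.
- *The trial is underpowered because of the t-test.* At 59 evaluable per group it is not. Section 1 recruits 177 children, which leaves about 53 per group after 10% loss, but that conflict with the 65 per group of section 6.1 is a separate matter.

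One could also answer that section 6.2 already mentions multiple regression and the imputation of covariates. The regression is exploratory, and neither statement changes the test of the lens effect. Because the protocol names that test, the point has not simply been left to a statistical analysis plan.

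**Conclusion.** The point holds as an efficiency improvement worth making. The protocol fixes an unadjusted primary test while it declares age stratification and collects the relevant baseline values. Whatever the allocation scheme, an adjusted analysis is at least as suitable and gains a few points of power if the covariates are prognostic. The size rests wholly on an assumed R². In the balanced case it further assumes that three age bands alone carry that R², so the upper end is generous. If part of it comes from baseline SER, which is not a stratification factor, the result lies between the two cases. Whether the t-test is conservative or merely less precise cannot be settled until sections 1 and 5.7 agree.

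**What to change.** 1. Reconcile sections 1 and 5.7 on how children are allocated: stratified with balance within age groups, or simple.
2. In sections 1 and 6.2, make the primary test a single ANCOVA of 12-month SER change on lens group (D2 against SV), with age stratum (4-6, 7-9, 10-12) and baseline SER of the analysed eye as covariates. Choose one form for age and state it. Use the same model for axial length change with baseline axial length in place of SER.
3. Report adjusted mean differences with confidence intervals, and keep the t-test as a sensitivity analysis.
4. Settle the model before the 6-month interim analysis, so that the choice cannot appear to follow the data.

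The cost is a few sentences. All covariates are already collected, the sample size can stay as it is, and the model spends three further degrees of freedom out of 116.
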